#### List of abbreviations

| **ABBREVIATION** | **DEFINITION** |
| --- | --- |
| ANI | Analgesia Nociception Index |
| ANSM | Agence Nationale de Sécurité du Médicament et des Produits de Santé (French Agency for the Safety of Medicines and Health Products) |
| ARC | Clinical Research Associate |
| ASA | American Society of Anestheology |
| CHRU | Regional University Hospital of Lille |
| CNIL | Commission Nationale de l'Informatique et des Libertés (French Data Protection Authority) |
| PPC | Comité de Protection des Personnes |
| CRF/eCRF | Case Report Form/ electronic Case Report Form |
| EI | Undesirable Event |
| EIG | Serious Undesirable Event |
| EVA | Visual Analog Scale |
| FC | Heart Rate |
| FDA | Food and Drug Administration |
| NOT | Systolic blood pressure |
| PK / PD | Pharmacokinetics / pharmacodynamic |
| Remi | Remifentanil |
| SNA | Autonomic Nervous System |
| VFC | Heart Rate Variability |

1. **SYNOPSIS**

| PROMOTEUR | **Lille University Hospital**  Health Research Department  [name] [contact] - [contact] |
| --- | --- |
| TITLE | Automatic ANI-guided remifentanil administration during propofol general anesthesia |
| PRINCIPAL INVESTIGATOR | [name] [name] |
| NUMBER OF CENTERS | 1 Center: Burns Treatment Center, Roger Salengro Hospital, Lille CHRU |
| TYPE OF STUDY | Controlled, Randomized, Single-blind, Class 1 single-center |
| OBJECTIVES | **Main objective**  To determine whether the ANI-loop medical device reduces the total amount of remifentanil (remi) administered compared with standard practice.  **Secondary objectives**  To determine whether automated administration of remifentanil by the ANI-loop device allows :   - improving hemodynamic stability during propofol general anesthesia. - increasing the time spent with an ANI between 50 and 70. - reducing immediate post-operative pain. |
| EXPERIMENTAL DESIGN | - category 1 randomized controlled trial - monocentric: Lille CHRU burn treatment center - randomization carried out by the Medical Promotion Department directly via the electronic CRF - in the *"ANI-loop"* arm, autonomous administration of remifentanil by the ANI-loop medical device (class IIb) under the supervision of an anesthetist - in the "standard practice" arm, administration of remifentanil adapted by the anaesthetist according to usual practice - ANI monitor visible on both arms |
| EVALUATION CRITERIA | **Main criterion:**  Total quantity of remi administered (value related to weight and duration of intervention).  **Secondary criteria to meet secondary objectives:**   - Proportion of time spent in hemodynamic reactivity, hypotension or bradycardia during the procedure. This proportion is equal to the cumulative duration of each episode of reactivity, hypotension or bradycardia, divided by the duration of the procedure. - Total dose of Ephedrine - ANIi and ANIm: proportion of time spent during |

|  | intervention in the following ranges: <50, [50-70], >70   - hypnotic component measurement index (BIS® or Entropie®): proportion of time spent during the procedure in the following intervals: <40, [40-60], >60 - ANI, heart rate, blood pressure, FetCO2, Pmax (ventilator) 5 min before start of procedure, 5 min after start of procedure and 20 min after start of procedure. - Pain assessed by visual analog scale (VAS) between H0 and H2, every 15 min.   Total quantity of morphine administered between end of surgery and H2 post-op.   - Total quantity of ketamine administered between end of surgery and H2 post-op.   -Frequency of postoperative nausea/vomiting assessed at H2.  Number of changes in remifentanil flow rate during the procedure   - Total quantity of propofol administered (absolute value, value related to weight, value related to weight and duration of procedure). - Number of propofol target changes during the procedure   In the *"ANI-loop"* arm only: number and total duration of disengagements of the ANI-loop device during the operation, i.e. the number of times and cumulative duration that the closed-loop system had to be interrupted and replaced by manual control as in the standard practical arm. |
| --- | --- |
| INCLUSION CRITERIA | - patients treated at the Lille CHRU Burn Treatment Centre - burn surgery: excision-grafting - age ≥ 18 years - informed consent - ASA I or II or III status - general anaesthesia with intubation and controlled assisted ventilation - body mass index between 17 and 40 kg.m-2 |
| NON-INCLUSION CRITERIA | - pregnant or breast-feeding women (simple questioning) - pace maker (regardless of operating mode) - non-sinus rhythm - heart transplantation - dysautonomia - diabetes mellitus with micro or macro angiopathic complications - foreseeable allergy or intolerance to a drug used in the study - baseline" hemodynamic measurements considered "reactivity", hypotension or bradycardia - FCbl>120 min^-1^ or PASbl>160 mmHg - uninsured - persons deprived of their liberty, in emergency situations, or persons incapable of consent and not benefiting from a legal protection regime (guardianship/curatorship) - unconscious or sedated patient before induction |
| NUMBER OF PARTICIPANTS | The aim of the study was to assess whether the ANI-loop medical device reduces the total amount of remifentanil administered compared with standard practice. On the basis of data in the literature [Leal PC et al.] and the usual practice of the |

|  | service, the total amount of remifentanil in the control group can be estimated at 0.30 ± 0.075 (mean ± standard deviation). To demonstrate a 20% reduction in the *ANI-loop* arm (i.e. a mean remifentanil quantity of 0.24 in the experimental group), with a first-species risk of 5% and a power of 80%, it is necessary to include 26 patients per group, for a total of 52 patients. |
| --- | --- |
| STATISTICAL ANALYSIS STRATEGY | Statistical analyses will be carried out using SAS software (version 9.4 or higher) and conducted at the Lille CHRU methodological support platform under the responsibility of [name]. To meet the primary objective, the total amount of remifentanil administered (value related to weight and duration of intervention) will be compared between the two study arms using a Student's t-test; the effect size will be calculated (standardized mean difference) with a 95% confidence interval. If the distribution of the primary endpoint deviates from normality, the Mann-Whitney U test will be used. |
| INVESTIGATION PROCEDURE SPECIFIC TO THE STUDY AND DIFFERENCES FROM USUAL CARE | - standard practice" arm: management is identical to that of total intravenous general anaesthesia - *ANI-loop"* arm: management differs from standard practice only in the administration of remi, which is administered via the ANI-loop device. |
| ASSESSING THE BENEFITS AND RISKS OF RESEARCH | PROFIT  Use of the device should result in more stable hemodynamics and therefore better anesthesia quality, as well as potentially lower total remi administration.  RISK   - standard practice" arm: the risk is identical to that of any general anaesthetic - *ANI-loop"* arm: in the event of failure of the ANI-loop device, the anesthetist can disengage it at any time and continue anesthetic management according to "standard practice" without delay. The risk is therefore comparable to that of the "standard practice" arm. |
| EXCLUSION PERIOD | Simultaneous participation in another study is prohibited, as it would run the risk of interacting with autonomic nervous system responses. This prohibition is limited to the duration of the study, i.e. the perioperative phase. |
| REASONS FOR SETTING UP OR NOT SETTING UP A SUPERVISORY COMMITTEE | No, in view of the similar risk in the *"ANI-loop"* arm and in the "standard practice" arm, the creation of a monitoring committee does not seem justified. |
| DURATION OF STUDY | - Length of inclusion period: 12 months - Duration of study participation for one subject: from arrival in the OR to H2 post-op. - Duration of research: 15 months - Data analysis time: 3 months |

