##### Secondary objectives and hypotheses

To determine whether the automated administration of remifentanil by the ANI-loop device allows:

- improving hemodynamic stability during propofol general anesthesia.
- increasing the time spent with an ANI between 50 and 70.
- reducing immediate post-operative pain.

In the *"ANI-loop*" arm only: determine whether ANI-loop enables fully automated administration (i.e. without the need to disengage the device).

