##### Evaluation criteria

- - 1. Definitions
- *baseline" values* for heart rate (HRbl) and systolic blood pressure (SBPbl) are the mean of 3 measurements taken before the start of anesthesia
- *hemodynamic reactivity*: HR > 120% of HRbl or SBP > 120% of SBPbl
- *hypotension*: PAS <75 mmHg
- *bradycardia*: HR < 40 min-1
- *intervention*: begins with skin preparation, includes surgery and ends with the end of dressing
  - 1. main criterion, making it possible to meet the main objective

Total quantity of remi administered (value related to weight and duration of intervention).

- - 1. secondary criteria to meet secondary objectives:

NB: several criteria are assessed after the patient wakes up, between extubation (H0) and H2 120 min after extubation. The patient does not need to be in the intensive care unit for this assessment; he/she can be in his/her hospital room.

- Proportion of time spent in hemodynamic reactivity, hypotension or bradycardia during the procedure. This proportion will be equal to the cumulative duration of each episode of reactivity, hypotension or bradycardia, divided by the duration of the procedure Total dose of Ephedrine.
- ANIi and ANIm: proportion of time spent during the intervention in the following intervals :

<50, [50-70], >70

- hypnotic component measurement index (BIS® or Entropie®): proportion of time spent during the procedure in the following intervals: <40, [40-60], >60
- ANI, heart rate, blood pressure, FetCO2, Pmax (ventilator) 5 min before start of procedure, 5 min after start of procedure and 20 min after start of procedure.
- Pain assessed by visual analog scale (VAS) between H0 and H2, every 15 min.
- Total quantity of morphine administered between end of surgery and H2 post-op.
- Total quantity of ketamine administered between end of surgery and H2 post-op.
- Frequency of postoperative nausea/vomiting assessed at H2.
- Number of changes in remifentanil flow rate during the procedure.
- Total quantity of propofol administered (absolute value, value related to weight, value related to weight and duration of procedure).
- Number of propofol target changes during the procedure.

In the *"ANI-loop"* arm only: number and total duration of disengagements of the ANI-loop device during the operation, i.e. the number of times and cumulative duration that the closed-loop system had to be interrupted and replaced by manual control, as in the standard practical arm.

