- propofol target adapted in both arms to maintain the hypnotic component index (BIS® or Entropy®) in the range [40-60]. During *the procedure*, propofol target changes will be made 1 minute after the last target change has become effective, and will follow the indications in table 1. This corresponds to the usual management in the burn unit of the Burn Treatment Center.

|  |  |  |
| --- | --- | --- |
| component  hypnotic | propofol target |  |
| >80 | + 2.0 |  |
| >60 | + 1.0 |  |
| <40 | - 0.5 |  |
| <25 | - 1.0 |  |
| **Table 1: Adaptation of propofol targets in both arms** | | |

|  |  |  |
| --- | --- | --- |
| ANI | target remi |  |
| <35 | + 2.0 |  |
| <50 | + 1.0 |  |
| >70 | - 0.5 |  |
| >90 | - 1.0 |  |
| **Table 2: Adaptation of remi targets in the "standard practice" arm** | | |

- remifentanil target
  - **in the *standard practice* arm**: increased to 4 ng.ml-1 at the start of *the procedure*, then adjusted to maintain ANI in the range [50-70] as indicated in Table 2. Target changes are made 1 minute after the last target change has become effective. This corresponds to usual management at the Burn Treatment Center.
  - **in the *ANI-loop* arm**, the automatic mode of the ANI-loop device is engaged at the start of *the procedure*. The flow of remifentanil is automatically regulated by the ANI-loop. The anaesthetist can switch to manual mode at any time in the event of inadequate regulation (device disengagement). The device is switched off at the end of the *procedure.*

Pre-emptive analgesia

- local infiltration of skin sample area with naropein 2 mg.ml-1 during

*intervention*

- paracetamol 1g IVL at end of *procedure*
- sufentanil 0.12 µg.kg-1 (max 10 µg) IVL at *end of procedure*

Prevention of postoperative nausea/vomiting

- ondansetron 4 mg IVL

Postoperative analgesia

- morphine titration according to Visual Analogue Scale (VAS), bolus of 3mg every 3 min (max 12mg)
- ketamine 20 mg IVL for persistent pain with VAS ≥ 40

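### The protocol calls the trial single-blind without saying who is blinded, and nothing keeps the arm from those who collect post-operative pain outcomes and give rescue analgesia

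*Protocol*

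**What the plan says.** The synopsis, under type of study, gives the design as "Controlled, Randomized, Single-blind". This is the only mention of blinding. Section 4.1 (Experimental design) describes the arms and the randomisation without repeating the label.

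Section 3.2 lists "reducing immediate post-operative pain" among the secondary objectives. Section 4.3 (Evaluation criteria) measures it in these ways:

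- "Pain assessed by visual analog scale (VAS) between H0 and H2, every 15 min", where H0 is extubation and H2 is 120 minutes later;
- "Total quantity of morphine administered between end of surgery and H2 post-op", with a matching criterion for ketamine.

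Nausea and vomiting are assessed at H2. On the place of assessment, section 4.3 says: "The patient does not need to be in the intensive care unit for this assessment; he/she can be in his/her hospital room".

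Section 5.2.3 (Anesthesia procedure) sets out rescue analgesia: "morphine titration according to Visual Analogue Scale (VAS), bolus of 3mg every 3 min (max 12mg" and "ketamine 20 mg IVL for persistent pain with VAS ≥ 40". It also has the anaesthetist supervise the loop, with the option of taking over manually, and has the device turned off when the procedure ends. Randomisation takes place through the eCRF in the operating room before induction. The section on data processing says that study data are entered in the eCRF and describes no restriction on who can see the allocation.

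**The concern.** A blinding label is useful only if the reader knows whom it covers. In its usual sense, single-blind means that the patient alone is unaware of the arm. On that reading the label gives no protection where staff collect an outcome or decide on a dose.

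The post-operative pain outcomes are of that kind. Someone obtains and records the VAS, and someone decides whether to give the next bolus. If that person knows that remifentanil was under automatic control, expectation may affect how the question is put, when it is asked, or whether a bolus is given. Expectation is unlikely to be neutral: section 2 presents the device as the local team's own innovation, and section 5.6 anticipates better anaesthesia from it.

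What is at stake is the credibility of one secondary objective. A difference in morphine use between the arms could reflect the device or the staff's knowledge of it, and the data could not separate the two. An analysis plan written later cannot repair this, because masking has to be in place at the bedside.

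**Working it through.** No formula gives the size of the bias, so the check is mainly a reading of the text. The one figure that can be reproduced is the sample size, which shows what the point leaves untouched.

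**1. The plan's own figure.** Section 4.4 assumes a control mean of 0.30, an SD of 0.075 and an experimental mean of 0.24, with 80% power. Section 4.5 sets a two-sided 5% level.

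- Standardised difference: (0.30 − 0.24) / 0.075 = 0.06 / 0.075 = 0.8.
- Normal approximation: 25 per arm.
- Two-sample t-test: 25.52, rounded up to 26 per arm; power at 26 is 80.7%.

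The stated 26 per arm, 52 in total, is reproduced. The primary endpoint is the amount of remifentanil related to weight and duration of the intervention. It is not a post-operative assessor's judgement, so nothing here changes alpha, power or the number of patients.

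**2. Who knows the arm, and who is said not to.**

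| Party | What the protocol says | Masked? |
| --- | --- | --- |
| Anaesthetist | Supervises the loop and may disengage it (5.2.3) | Cannot be |
| Patient | Allocation is made in the operating room before induction (5.2.3); unconscious or sedated patients are not included (4.2) | Possible, but no instruction |
| Person collecting VAS and nausea/vomiting | Not identified (4.3) | Not stated |
| Person giving morphine and ketamine | Not identified (5.2.3) | Not stated |
| eCRF users | Allocation and outcome data are in the same system | No restricted view described |

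**3. How far each outcome depends on staff.**

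- *VAS.* Every 15 minutes over 120 minutes gives 120 / 15 + 1 = 9 readings if both ends count. The protocol does not say who scores. If the patient does so and is blinded, what remains is prompting, timing and recording.
- *Morphine.* Bolus, interval and maximum are fixed, but the text gives no VAS value at which titration begins. Staff discretion therefore enters the endpoint directly.
- *Ketamine.* A VAS value is written, but whether pain counts as persistent is a judgement.
- *Nausea and vomiting.* Recorded at H2 by an unnamed person.

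**4. Whether masking is possible.** The device is off before H0, and section 4.3 allows the assessment in the patient's own room. The reason why the anaesthetist cannot be blinded no longer applies by then, provided that the assessor was not in theatre.

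**5. What masking from H0 cannot reach.** The morphine and ketamine totals start at the end of surgery, before extubation. Doses in that interval may be given by the theatre team.

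**The case against.** The strongest reply is that the document is silent and silence is not a failure. A reader might infer that recovery staff know the arm. No section says so, and none says that device details are passed on at handover. This stands: the defect is a missing safeguard, not a documented breach.

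Second, single-blind conventionally promises nothing about assessors, so there is no contradiction with the label. This also stands. Patient blinding is plausible, since automatic mode runs only under anaesthesia and the ANI display is visible in both arms. The label is still undefined, and on its usual reading the staff are left unmasked.

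Third, a reader might infer that staff score the VAS, or that VAS and rescue totals would be biased in the same direction. Neither is supported. The scorer is not named. Prompting lower scores would lower both measures, whereas giving boluses more freely would raise morphine and could lower later scores.

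Fourth, a reader might take one 3 mg bolus against the 12 mg maximum, 3 / 12 = 25%, as the size of the problem. It is not a bias estimate, because it says nothing about how often a bolus would change or about any difference between the arms.

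Fifth, staffing is not described. In a single burn centre the assessor may be the anaesthetist, and masking would then not be free. This stands and limits the fix. The section on participating teams (5.1) and the consent pages are not in the available text, so relevant wording there cannot be ruled out.

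Finally, withholding the intraoperative record from people who titrate opioids would touch clinical care. That is a fair objection to such a measure, and it is not needed: the control mode alone can be left out.

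**Conclusion.** The point holds as a gap in the design as written. The protocol uses a blinding label without saying whom it covers, and it fixes nothing to keep the arm from those who collect VAS and nausea/vomiting or give rescue analgesia up to H2. The objective on immediate post-operative pain is therefore open to avoidable performance and assessment bias.

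The size and direction of that bias are unknown and cannot be derived from the document. Exposure is greatest for the morphine total. It is less for VAS if the patient is masked and rates it unaided. The primary endpoint and the sample size are not affected. It does not follow that the pain results would be worthless.

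The conclusion rests on two assumptions: that the text not available contains no masking provision, and that at least some assessments between H0 and H2 are made by people who were not in theatre. If the second fails, masking those assessors is not feasible without other staff, and the remaining remedy is to report these outcomes as open-label. This is an inexpensive improvement that should be made, not a flaw that threatens the trial.

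**What to change.** Add to section 4.1 a statement of who is blinded and until when:

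- The patient is not told the arm up to H2, and the allocation is not announced while the patient is awake in the operating room.
- Where they are not the theatre team, the existing staff who record VAS and nausea/vomiting and give rescue analgesia from H0 to H2 are not told the arm.
- The handover omits only whether remifentanil was controlled by ANI-loop or manually. All clinical information, including drugs and doses given, stays available.
- The allocation is hidden in those staff's eCRF view.
- Where the assessor took part in the anaesthesia or learns the arm, this is recorded and the outcomes concerned are reported as open-label.

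No dose or treatment rule changes. The cost is a short protocol addition, an eCRF access setting and some care at handover. Masking will be incomplete, especially for doses given between the end of surgery and H0, and the report should say so.

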#### Rational: Scientific justification and general description of the research

Pain management in the hospital environment is an integral part of improving the quality of care. The difficulty for caregivers lies in assessing the level of pain in order to adapt prescriptions and limit the risk of adverse effects from these drugs^1^ . General anesthesia combines hypnotic and analgesic drugs to enable surgical procedures to be performed. The clinical and paraclinical data, such as pulse and blood pressure, used to monitor patients under general anesthesia do not enable us to accurately anticipate patients' analgesic requirements. What's more, the potent drugs used expose patients to the ever-present risk of overdosing, making it necessary to seek out the minimum doses required for the surgical procedure. On the other hand, inadequate analgesia could have cardiovascular repercussions (in particular, increased heart rate or blood pressure), which would be detrimental to the surgical procedure (increased bleeding) and could lead to heart attacks in coronary patients, as well as complications during the recovery phase (pain, anxiety). The quality of anesthesia depends on the optimal use of anesthetic products, which prevent the patient, even when unconscious, from feeling the pain associated with surgery. The search for the minimum effective dose of analgesics is also a major objective of modern anesthesia, in order to limit the risk of post-operative hyperalgesia^2,3^ . Optimizing the administration of analgesics can be expected to improve recovery conditions and reduce the risk of peri-operative complications, which could contribute to the evolution of clinical practices in favor of shorter hospital stays.

Studies have clearly demonstrated that cardiovascular regulatory processes are closely linked to pain perception. Heart rate variability (HRV) analysis is a well-known, non-invasive method for measuring the regulation of the cardiovascular system by the autonomic nervous system (ANS). This analysis is based on the principle that heart rate fluctuations reflect the activity of the sympathetic and parasympathetic systems, the main components of the ANS^4^ . Studies have shown that heart rate fluctuations above 0.15 Hz are exclusively due to the influence of the parasympathetic system. In adults, painful, fearful or anxious phenomena are accompanied by a decrease in high-frequency HRV (>0.15 Hz), indicating a reduction in parasympathetic tone during unpleasant stimuli or emotions. During surgery, HRV analysis correlates with the balance between nociception and analgesia. In children, a significant decrease in high-frequency spectral power has been observed during painful surgical procedures, suggesting a reduction in parasympathetic influence during the nociceptive stimulus. The Lille team, which includes clinicians and scientists associated with the Clinical Investigation Center - Technological Innovation (INSERM CIC-IT 1403) at the Lille CHRU, has been working on HRV analysis for several years. This work has led to the creation of an original HRV index linked to the analgesia-nociception balance: the ANI (Analgesia Nociception Index). This technology has been the subject of several patent applications. This technology is now available through the Physiodoloris® device (Mdoloris Medical Systems®, Loos, France). This CE-marked medical device is currently in routine clinical use in numerous hospitals .^5-9^

Recent studies have shown that using the Physiodoloris® device to adapt the analgesic component of general anaesthesia can limit the occurrence and duration of reactive episodes that are deleterious to the patient, while significantly reducing intraoperative morphine consumption. In most of these studies, the aim was to regulate remifentanil administration by manually changing the flow rate of the syringe pump according to the displayed ANI values. Thanks to our experience in the use of ANI during general anesthesia, we have established various decision rules based on ANI and blood pressure analysis, to guide the anesthetist in the management of intraoperative analgesia.

Our latest innovation is a medical device that automates the administration of remifentanil according to a pre-established algorithm. Two patents have been filed for this innovation. The ANI-loop medical device takes the form of a controller implemented on a microcomputer, connected to the multiparameter scope used for anesthesia monitoring, as well as to the Physioldoloris® monitor and an electric syringe pump (Appendix I).

We propose to conduct a randomized controlled trial to determine whether use of the ANI-loop medical device during propofol general anesthesia reduces the total dose of remifentanil administered.

